### Data analysis

All statistical analyses will be performed by full-time statisticians using R Studio (Version 1.2.5001, R Studio Inc., Boston, MA, USA). The normality test will be used to determine whether the data are normally distributed. Continuous variables with a normal distribution will be reported as the mean ± SD, and ordinal and non-normally distributed variables will be reported as the median and interquartile range. Independent samples t-tests or Mann-Whitney U-tests will be used for comparisons, as appropriate. Categorical variables will be reported as counts and proportions, and the Pearson χ^2^ test or Fisher’s exact test will be used for comparisons, as appropriate.

The primary outcomes (remission rate 3 months after drug withdrawal and after 1 year of follow-up) will be compared between groups using Pearson’s χ^2^ test or Fisher’s exact test. Logistic regression will be used to adjust for potential confounders. Variables with P < 0.05 in the univariate comparisons, and known confounders that could impact the efficacy, will be included in the multivariable logistic regression models.

Subgroup analyses will be conducted of the primary outcomes stratified by age group (young, 18 ~ 35 years; middle-aged, 36 ~ 59 years; older, 60 ~ 65 years); duration of disease (<1 year, 1 ~ 2 years, 2 ~ 3 years); BMI (18.5 ~ 27.9 kg/m^2^, 28 ~ 40 kg/m^2^); and sex, using the same methods of analysis.

For the secondary outcomes, continuous data will be analyzed using the linear mixed effects model, which will use the random intercept model to explain the internal correlation of participants. Discontinuous data will be analyzed similar, but the generalized linear model appropriate to the distribution assumptions and link functions will be used. The analysis of all secondary outcome indicators also corrected for potential confounders (including variables with P < 0.05 in the univariate comparisons and known confounders that could have an impact on the efficacy). The safety indicators will be analyzed using the same methods used to analyze the main outcome indicators.

Missing values will be filled using multiple imputation methods, and sensitivity analyses will be performed.

Two-tailed P-values will be used, and P-values < 0.05 will be regarded as statistically significant. Point estimates will be reported with 95% confidence intervals.

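### The subgroup plan compares the arms inside each of ten strata at P < 0.05, which does not test whether the treatment effect differs between strata

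*Protocol article*

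**What the plan says.** All of this stands in the Data analysis section of the protocol article.

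- Subgroup analyses: "Subgroup analyses will be conducted of the primary outcomes stratified by age group" and three further factors.
- Subgroup factors: "stratified by age group (young, 18 ~ 35 years; middle-aged, 36 ~ 59 years; older, 60 ~ 65 years"), then "duration of disease (<1 year, 1 ~ 2 years, 2 ~ 3 years"), then BMI in two bands, "and sex, using the same methods of analysis".
- The methods carried over are those of the main analysis. The arms "will be compared between groups using Pearson’s χ^2^ test or Fisher’s exact test", and "Logistic regression will be used to adjust for potential confounders". Covariates enter that model if they reach P < 0.05 in univariate comparisons or are known confounders.
- The outcomes are plural: "The primary outcomes (remission rate 3 months after drug withdrawal and after 1 year of follow-up").
- The only decision rule is: "Two-tailed P-values will be used, and P-values < 0.05 will be regarded as statistically significant". Point estimates are to carry 95% confidence intervals.

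The section names no treatment-by-subgroup term. It gives no expected subgroup sizes and no rule for interpreting subgroup results.

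**The concern.** A subgroup analysis is normally meant to show whether the treatment effect varies with a patient characteristic. The stated method answers another question, namely whether the arms differ within this stratum. A significant result in one stratum beside a non-significant one in its neighbour is no evidence that the two effects differ. The pattern arises readily by chance, from unequal stratum sizes, or because each stratum has low power.

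Two practical problems follow. Many tests are run at an unadjusted 0.05, so an isolated positive result is fairly likely even if the drugs are equivalent. And the covariate-selected logistic model is to be refitted in strata that may hold few remissions. At stake is the soundness of any statement that canagliflozin does better or worse than metformin in a given age, duration, BMI or sex group.

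**Working it through.** The article gives no subgroup figure to reproduce, so the check builds on its stated inputs.

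**Inputs.** From Data analysis: 3 age, 3 duration, 2 BMI and 2 sex strata; two time points; two-sided 0.05. From Sample size calculation: remission 20.9% in both arms; 73 per group needed and 92 enrolled, so 146 to 184 in total. (Whether 73 follows from the stated margin is a separate matter.) Stratum shares are not given and are assumed below.

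**1. Number of tests.** 3 + 3 + 2 + 2 = 10 strata; 10 × 2 time points = 20 unadjusted arm comparisons. The logistic models come on top and are not counted.

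**2. Chance of at least one P < 0.05 with no effect anywhere.**
- If the tests were independent: 1 − 0.95^10 = 40.1% at one time point; 1 − 0.95^20 = 64.2% over both. These are upper figures, because every participant appears in all four factors and the two time points are correlated.
- Simulated with overlapping strata, using chi-square, or Fisher's test when an expected count is below 5. One-year remission is 20.9% in both arms. Three-month remission is 0.209 + 0.791 × 0.115 = 30.0% (assumed). Strata are either even or uneven (assumed: age 20/65/15%, duration 60/25/15%, BMI 70/30%, sex 50/50%). For 184 participants: about 27–32% at one time point and 41–46% over both. For 146 participants with uneven strata it falls to about a quarter and just under 40%.

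**3. Stratum sizes, if evenly split.**
- Age and duration: 73/3 = 24 to 92/3 = 31 per arm; × 0.209 gives 5 to 6 expected remissions per arm, or about 10–13 in the whole stratum.
- BMI and sex: 73/2 = 37 to 92/2 = 46 per arm; × 0.209 gives 8 to 10 per arm.
- As an illustration, suppose the logistic model held treatment plus the five balancing factors listed under Randomisation and interventions (age, sex, HbA1c, BMI, disease course). That is 6 parameters, so an age or duration stratum would have 10/6 = 1.7 to 13/6 = 2.2 remissions per parameter.

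**4. What a uniform true effect would look like.** Assume 20.9% against 40.9% in every stratum (an illustration; the article plans on equal rates). Power per stratum is about 32–40% at 24–31 per arm and 46–55% at 37–46 per arm. The strata of one factor share no participants, so the chance of a mixed pattern, with some strata significant and others not, is:
- three-level factor: 1 − p³ − (1 − p)³ = 65% at p = 0.319 and 72% at p = 0.397;
- two-level factor: 2p(1 − p) = 50% at p = 0.46 and at p = 0.547.

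So even when the effect is identical everywhere, a mixed pattern is as likely as not, or more likely.

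**5. One interaction test per factor.** 4 tests per time point instead of 10. Under independence: 1 − 0.95^4 = 18.5% against 40.1%; over both time points 1 − 0.95^8 = 33.7% against 64.2%.

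**The case against.** The strongest reply is that interaction tests, multiplicity handling and an exploratory label are commonly left to a statistical analysis plan, and this is a condensed article. That is right as far as it goes: their absence alone would be no finding. But the article does name a subgroup method, and a plan that followed it would test within strata. Within-stratum comparison is acceptable as description, and nothing in the text forbids a later interaction test. The difficulty is that it is the only method named and carries the 0.05 rule.

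Other parts of the defence stand. The four factors are prespecified, with cut-points for age, duration and BMI, which limits selection after the fact. Confidence intervals are already promised, and Fisher's test is available for sparse tables.

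A reader might also infer more than the documents support:
- That stratum results will be reported as differential remission. No such rule is stated, and Study objectives contains no subgroup objective. Misreading is a risk, not a plan.
- That the Background expects the treatment effect to vary with disease duration. It says a shorter course makes remission more likely. That is prognostic and says nothing about the difference between the drugs.
- That all ten groups are tiny. No sizes are given, and the BMI and sex strata would be moderate if evenly split. Small is fair for age and duration, and the youngest and oldest age bands could be smaller still.
- That the false-positive risk is 40% or 64%. Those figures assume independence.

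**Conclusion.** The point holds in limited form. The article fixes a subgroup method that cannot show whether the treatment effect differs between strata, and repeats it in ten strata at two time points with an unadjusted 0.05 threshold. The realistic chance of at least one spurious significant result is roughly three in ten at one time point and somewhat above four in ten over both, given the assumed stratum shares and 30% three-month rate. The doubt about the logistic model applies to the age and duration strata under an even split, and depends on how many covariates are selected, which the article does not state. Severity is minor: the main comparison, the sample size and the safety analyses are not touched.

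**What to change.** Replace the within-stratum significance tests by one treatment-by-factor interaction test for each of age, duration, BMI and sex: 4 per time point instead of 10. Report the effect estimate with its 95% confidence interval in each stratum, without calling any stratum significant, and label the subgroup analyses exploratory.

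The cost is a change of wording in the analysis plan and slightly different code; no new data are needed. Two limits should be stated with it. Interaction tests have low power at this sample size, so a non-significant interaction must not be read as showing equal effects. And four tests still carry a false-positive chance of 18.5% per time point if independent, which is why the exploratory label is needed.

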### Randomisation and interventions

A total of 184 participants will be randomly allocated to receive either canagliflozin or metformin treatment (1:1). The randomization operation will be generated by an independent statistician, who will ensure the balance of participants according to age, sex, HbA1c and BMI and course of their disease when grouping, and a code list will be directly allocated to the main investigators of every center. The intervention content of the two groups is as follows.

Canagliflozin treatment group: For oral treatment, the participants will receive canagliflozin tablets (Janssen-Cilag S.p.A., Ltd., National Drug Approval: H20170375) once daily, 100–300 mg per time, with a minimum dose of 100 mg per day and maximum dose of 300 mg per day.Metformin treatment group: For oral treatment, the participants will receive metformin hydrochloride tablets (Sino-American Shanghai Squibb Pharmaceutical Co., Ltd., National Drug Approval: H20023370 (0.5 g × 20 tablets)/Sino-American Shanghai Squibb Pharmaceutical Co., Ltd., National Drug Approval: H20023371 (0.85 g × 10 tablets × 2 plates)), 1–3 times a day, 500–2000 mg per time, with a minimum dose of 500 mg per day and maximum dose of 2550 mg per day.

Regarding weekly titration for oral drug metering, the titration targets are fasting blood glucose (FBG) (3.9–5.6 mmol/L) and blood glucose at 2 h after each of the three meals (5.0–7.0 mmol/L). After meeting the above criteria, the participants will continue the medication for 3 months and then stop.

Routine diabetes health education will be provided to all participants during the treatment period. Routine diet control and appropriate exercises will be planned. Follow-up will be conducted monthly for the first 3 months after the end of treatment and every 3 months thereafter for 1 year (Table 1; Fig. 2). Participants with FBG > 7.0 mmol/L and postprandial blood glucose (PBG) > 10 mmol/L during the follow-up period are defined as having hyperglycemia recurrence, which will be treated according to the Chinese guidelines for the diagnosis and treatment of T2DM and is defined as not remitted.

**Table 1 Tab1:** Participant visit schedule

**Research Stage**	**Screening**	**Baseline**	**Intervention Period**				**Follow-up Period**		

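### A random intercept with ordinary residuals assumes equal variance and correlation across on-drug and off-drug visits, so visit-specific and change contrasts of glycaemic secondary outcomes may have miscalibrated intervals

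*Protocol article*

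**What the plan says.** The Data analysis section of the protocol article sets the method: "For the secondary outcomes, continuous data will be analyzed using the linear mixed effects model", a model "which will use the random intercept model to explain the internal correlation of participants". It mentions no random slope and no other device for within-participant correlation. It does not state the residual covariance, the visit and group-by-visit terms, the contrasts to be reported, or the type of standard error.

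Randomisation and interventions describes the series these outcomes are measured over. Doses are titrated weekly to common fasting (3.9–5.6 mmol/L) and 2-hour (5.0–7.0 mmol/L) glucose targets. "After meeting the above criteria, the participants will continue the medication for 3 months and then stop". Then: "Follow-up will be conducted monthly for the first 3 months after the end of treatment and every 3 months thereafter for 1 year". Recurrent hyperglycaemia during follow-up is a condition "which will be treated according to the Chinese guidelines for the diagnosis and treatment of T2DM and is defined as not remitted". Worsening blood glucose is listed under Exit and withdrawal criteria.

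The primary outcome is handled separately. Remission rates "will be compared between groups using Pearson’s χ^2^ test or Fisher’s exact test", with logistic regression for adjustment.

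**The concern.** A random intercept with independent, equal-variance residuals is compound symmetry: the same variance at each visit, and the same correlation whether two visits are three months or more than a year apart. The design gives reason to doubt both for glycaemic outcomes. Everyone is brought to the same narrow glucose range before stopping, which tends to compress spread on drug. Off drug, participants divide into those who stay in remission and those who relapse; the sample size section plans on 20.9% remission in each arm. The series also crosses a drug withdrawal, so correlation with baseline may well fade.

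If the assumption fails, the model applies an average variance and an average covariance to every visit. A contrast at a visit with above-average spread gets too small a standard error, and one at a visit with below-average spread gets too large a one. HbA1c, glucose, insulin and the HOMA indices serve the secondary objective on mechanism and will be judged at P < 0.05 with 95% intervals. False positives late in follow-up, or lost precision at withdrawal, would bear on that objective.

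**Working it through.** **Inputs.** The plan gives no design figure for this model, so there is none to reproduce. The 73 evaluable participants per group come from the sample size section and were set for the remission rate. They serve here only as an illustrative n, which cancels from the ratio of standard errors and so does not drive the error rates. Six time points are assumed: baseline, withdrawal, and months 3, 6, 9 and 12. All SDs and correlations below are assumptions.

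**Formulas.** For complete balanced data with group-by-visit means, with V the mean visit variance and C the mean between-visit covariance:
- model SE of a group difference at any visit = √(2V/n); true SE at visit j = √(2·SD_j²/n);
- model SE of a difference in change = √(4(V − C)/n);
- type I error = 2[1 − Φ(1.96 × model SE / true SE)].

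**1. Rising spread.** SDs 0.8, 0.4, 0.6, 0.8, 1.0, 1.2.
- V = (0.64 + 0.16 + 0.36 + 0.64 + 1.00 + 1.44)/6 = 4.24/6 = 0.707.
- Model SE = √(2 × 0.707/73) = 0.139 at every visit.
- True SE at month 12 = √(2 × 1.44/73) = 0.199; at withdrawal = √(2 × 0.16/73) = 0.066.
- Month 12: ratio 0.139/0.199 = 0.70, and 1.96 × 0.70 = 1.37, so type I error is about 17% and coverage about 83%.
- At withdrawal the model SE is about 2.1 times the true one.

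A 200-replicate simulation with a fitted random-intercept model gave 14% at month 12 and 0% at withdrawal. The Monte Carlo SE of the 14% is √(0.14 × 0.86/200) ≈ 2.5 points, so the two results agree.

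**2. Equal spread, decaying correlation.** All SDs equal, correlation 0.8 per visit step.
- Mean pairwise correlation = (5×0.8 + 4×0.64 + 3×0.512 + 2×0.4096 + 0.3277)/15 = 9.243/15 = 0.616.
- Baseline-to-month-12 correlation = 0.8⁵ = 0.328.
- SE ratio for change = √[(1 − 0.616)/(1 − 0.328)] = 0.756; 1.96 × 0.756 = 1.48; type I error about 14%.

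**3. Sensitivity to the pattern.** Coverage of nominal 95% intervals was simulated (4,000 runs, 73 per group, closed-form compound-symmetry fit; Monte Carlo SE about 0.3 points near 95%). Correlation is 0.8 per step except in the first row, where it is a constant 0.6.

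| SDs (baseline, withdrawal, months 3, 6, 9, 12) | Withdrawal | Month 12 | Change to month 12 |
|---|---|---|---|
| all equal, constant correlation | 94.3% | 94.7% | 94.8% |
| all equal | 95.0% | 94.8% | 85.8% |
| 1, 0.7, 0.8, 0.9, 1, 1.1 (mild rise) | 98.6% | 89.4% | 82.1% |
| 1, 0.5, 0.8, 1, 1.2, 1.4 (strong rise) | 100.0% | 84.7% | 81.6% |
| 1, 0.6, 0.9, 1.0, 0.8, 0.6 (rise, then fall) | 99.2% | 99.4% | 87.4% |
| 1, 1.0, 0.9, 0.8, 0.8, 0.8 (higher at withdrawal) | 92.0% | 96.8% | 85.6% |

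With equal SDs the single-visit intervals are correct. With rising SDs month-12 intervals are too narrow. If the spread falls again, they are too wide at both visits. If spread is larger at withdrawal, the direction reverses.

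**4. Effect averaged over visits.** The true variance of a participant's mean over K visits is [V + (K − 1)C]/K. Compound symmetry estimates exactly V and C, so with complete data a group effect averaged over all visits is unaffected.

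**The case against.** A reader might infer that month-12 intervals are too narrow and withdrawal intervals too wide as a matter of fact. The documents do not support that: no visit SD or correlation appears in them, and every size above follows from assumed values. Treatment of recurrence and exit for worsening glucose both act on the upper tail that would widen late spread. This objection stands, and it is why the direction is stated only conditionally.

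The article fixes the random-effects part but not the residual part. A random-intercept model can carry visit-specific residual variances, serial correlation or robust standard errors, and a separate analysis plan may specify them. This stands in part. The sentence still presents the random intercept as the way within-participant correlation is handled, and read in the ordinary way that means compound symmetry.

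The article also does not say that contrasts at single visits or changes from baseline will be reported, and an average over visits would be sound with complete data. That limits the harm to the contrasts named.

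The titration argument concerns glycaemic measures. Weight, blood pressure and lipids are covered by the same model but not titrated to a target, so rising spread cannot be presumed for them.

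Against this, the glycaemic design makes equal variance hard to defend. Fasting glucose confined to 3.9–5.6 mmol/L has an SD of at most 1.7/2 = 0.85 mmol/L (1.7/√12 = 0.49 if uniform), while off drug the plan expects a mixture of remitters and relapsers. The bound applies when the target is met and does not by itself give the SD at withdrawal.

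**Conclusion.** The point holds in conditional form. The named model, with ordinary residuals, imposes equal variance and equal correlation on a series for which neither is plausible in glycaemic outcomes. Contrasts at one visit, or for change from baseline, would then be miscalibrated. Illustrative type I error at month 12 is about 10–17% if spread rises off drug, and about 14% for baseline-to-month-12 change if spread is equal and correlation decays at 0.8 per step. The direction differs if late variance shrinks.

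It would also be wrong to infer that the remission result is at risk: that analysis uses Pearson's χ² or Fisher's exact test and logistic regression. The consequence is confined to continuous secondary outcomes, mainly the glycaemic ones. A change is worth making because it is cheap and protects the intervals under every variance and correlation pattern considered.

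**What to change.** For continuous secondary outcomes, replace the random-intercept sentence with a mixed model for repeated measures: treatment, visit, treatment-by-visit and the baseline value as fixed effects, and an unstructured within-participant covariance. If that does not converge, use a simpler structure with visit-specific variances and robust standard errors.

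The cost is one sentence and more covariance parameters: 5×6/2 = 15 for five visits or 6×7/2 = 21 for six, which 184 participants can support. Late-visit intervals may be wider where spread has in fact grown. If variances and correlations turn out equal, little is lost.

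### Safety is assigned to tests for proportions that ignore exposure, although time on drug varies with response and is followed by 12 months off drug

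*Protocol article*

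**What the plan says.** Data analysis compares the primary outcome between groups by Pearson's chi-square test or Fisher's exact test, and adds: "Logistic regression will be used to adjust for potential confounders". Covariates are those with P < 0.05 in univariate comparisons and known confounders of efficacy. No term for time on drug is named. Safety then receives one sentence: "The safety indicators will be analyzed using the same methods used to analyze the main outcome indicators".

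Three other parts of the article bear on whether that choice fits:

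- **Time on drug (Randomisation and interventions).** Doses are titrated weekly towards fasting and post-meal glucose targets. No maximum length of titration is given. "After meeting the above criteria, the participants will continue the medication for 3 months and then stop".
- **Time off drug (same section, and Table 1).** Follow-up runs for 1 year after treatment ends. Hyperglycaemia recurring in that year is a condition "which will be treated according to the Chinese guidelines for the diagnosis and treatment of T2DM".
- **Safety data (Safety outcomes; Follow-up visit).** Adverse events are sought by monthly telephone contact, with examinations every three months. The Follow-up visit section gives the same pattern of contact for the period after drug withdrawal. The monitored items mix incidences (hypoglycaemia, ketosis, cardiovascular and cerebrovascular events) with continuous measures (vital signs, electrolytes, eGFR, urinary albumin/creatinine ratio).

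**The concern.** The remission outcome is a yes/no status with the same meaning for every participant, so a comparison of proportions suits it. Adverse events arise over time, and here the time at risk on drug is not fixed by design. It lasts as long as a participant takes to reach target, plus 3 months. If one drug brings participants to target sooner, its arm has less on-drug time in which to record events. A crude proportion treats the two exposures as equal.

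The on-drug period is also followed by a longer off-drug period in which adverse events are still collected and some participants start other glucose-lowering treatment. The sentence on safety does not separate these periods.

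At stake is whether a reported difference in hypoglycaemia, ketosis or another event reflects the drugs or only the time spent on them, and whether a real on-drug difference remains visible.

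There is a further mismatch for the continuous indexes. The primary outcome is binary, so its methods apply to a laboratory value only after that value has been cut into categories. The opening of Data analysis offers t-tests or Mann-Whitney tests for continuous variables, and mixed models are given to continuous secondary outcomes, but the safety sentence points to neither.

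**Working it through.** The article gives no safety figure to reproduce. The checks below are illustrations; every rate and titration length in them is an assumption.

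**Inputs from the article:** 3 months on drug after reaching target; 12 months off drug; 92 participants enrolled per arm.

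**Assumptions:** titration of 1 versus 3 months, or a range of 4 to 12 weeks; event rates constant over time.

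**Step 1. Unequal exposure, no true difference in rate.** Let the rate be 0.03 per person-month in both arms. The risk over m months is 1 − exp(−0.03 m).

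- Titration 1 month, so 4 months on drug: 1 − exp(−0.12) = 11.3%.
- Titration 3 months, so 6 months on drug: 1 − exp(−0.18) = 16.5%.

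The apparent risk ratio is 16.5/11.3 = 1.46 although the rates are equal. This step uses on-drug time only and does not depend on how the off-drug year is handled.

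**Step 2. Share of observed time on drug.** Taking 3 months as 13 weeks and the off-drug year as 52 weeks:

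- Titration 4 weeks: 17/(17 + 52) = 0.246, about 25%.
- Titration 12 weeks: 25/(25 + 52) = 0.325, about 32%.

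The share rises as titration lengthens. At 6 months of titration it is 9/21 = 43%.

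**Step 3. Dilution if the whole period is counted.** Let f be the on-drug share, 2 the true on-drug rate ratio, and k the off-drug rate in both arms as a fraction of the control on-drug rate. The pooled ratio is [2f + k(1 − f)] / [f + k(1 − f)].

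- k = 1: the ratio is 1 + f, or about 1.25 to 1.32.
- k = 0.1, f = 0.25: (0.50 + 0.075)/(0.25 + 0.075) = 1.77.
- k = 0: the ratio stays at 2.0.

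**Step 4. The same effect as proportions and power.** Assume 3% versus 1% per month on drug, 1% per month in both arms off drug, and 1 month of titration.

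| Period counted | Higher-rate arm | Other arm | Risk ratio | Power, 92 per arm |
|---|---|---|---|---|
| On drug, 4 months | 1 − exp(−0.12) = 11.3% | 1 − exp(−0.04) = 3.9% | 2.9 | 47% |
| Whole, 16 months | 1 − exp(−0.24) = 21.3% | 1 − exp(−0.16) = 14.8% | 1.4 | 21% |

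This table also takes k = 1, the case with the most dilution among those in Step 3.

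**The case against.** The strongest reply is that the safety sentence names tests, not a period. A Fisher test works inside an on-drug window as well as outside it. The window, the definition of a treatment-emergent event and the handling of rescue treatment are commonly left to a full protocol or analysis plan, and neither is shown. That stands: their absence from a condensed article is not a finding. What the article does state is the method, and that method has no exposure term whichever window is later chosen.

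Second, time to target is itself a consequence of the assigned drug, so participants with an event by randomised arm is a legitimate comparison of treatment strategies. That also stands, and it is why the proportion should be kept beside the rate. It cannot, however, tell a more harmful drug from one that was merely taken for longer.

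Third, the dilution figure depends on its assumptions. It needs the whole period to be counted and an off-drug rate as high as the control on-drug rate. For events caused by the drug, the off-drug rate may be far lower and the dilution small, as Step 3 shows. Some participants with recurrence may also leave early, since worsening glucose is listed under Exit and withdrawal criteria.

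Some stronger readings are tempting but not supported:

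- *Safety is assessed at the two remission time points.* The phrase "remission rate 3 months after drug withdrawal and after 1 year of follow-up" defines the primary outcomes and is not carried over to safety.
- *The plan pools on-drug and off-drug events.* No section says so. The article only fails to separate them.
- *Dilution could reverse the safety conclusion.* Equal off-drug rates pull a ratio towards 1 and cannot carry it past 1.
- *Participants will receive the other arm's drug after recurrence.* The article refers to national guidelines and names no agent, so this is possible but not stated.

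**Conclusion.** The point holds in a limited form. The article fixes for safety a set of methods that take no account of exposure, in a design where time on drug depends on response, has no stated upper limit and can differ between arms. Unequal exposure alone could create or mask a difference. With an equal assumed rate of 3% per month, two extra months on drug move the risk from 11.3% to 16.5%. This part needs no assumption about pooling.

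Dilution by the off-drug year is conditional. If all observed time is counted, a rate ratio of 2 could appear as anything from about 1.25 (4 weeks of titration, off-drug rate equal to the control on-drug rate) to nearly 2 (off-drug events rare). The article settles neither the window nor the rates.

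For continuous laboratory and vital-sign indexes, tests for proportions are the wrong tool whatever the window. The change is worth making before recruitment, but it concerns analysis wording and reporting rather than the conduct of the trial.

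**What to change.** Replace the sentence on safety in Data analysis with wording to this effect: the main safety comparison will cover an on-drug window, from first dose to last dose plus a number of days that the sponsor fixes in advance. It will be reported both as participants with at least one event and as events per person-time. The off-drug year will be reported separately, split at the start of any treatment for recurrence. Continuous laboratory and vital-sign indexes will be analysed as change from baseline.

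The cost is analysis wording and one extra set of safety tables. The analysis needs dates of dosing, of events and of the start of recurrence treatment. These should be obtainable from the planned visits and the participant diary, which already records medication and adverse reactions. The drawback is fewer events in the on-drug window and so wider intervals.
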